### Next several visits for treatment (two sessions per week until the completion of eight sessions)

The same treatment will be repeated according to group. In the last session, blood samples will be drawn 5 min after the treatment completion, at the same time of day as the previous extraction.

### At 1 month’s time

The interviewers will repeat the assessments for pain level, analgesic consumption, and the type of treatment that the patient believes he or she is receiving as well as the assessment by the WOMAC scale and the GADS. The patient will once again answer the quality-of-life questionnaire (SF-36v2). Once the forms have been completed, treatment will be administered to the patient.

### Subsequent visits

At 3 and 6 months after treatment start and at the final visit, the questionnaires again will be filled out. The interviewers will also note EA-related adverse effects or complications observed either by the participants or by the acupuncturist throughout the duration of the treatment. Treatments will be performed each month up until the third month, and after this latter treatment session, with just one treatment every 45 days until the sixth month. Finally, a treatment will occur every 2 months until the study is completed at the end of 1 year. Blood tests will be performed again on the third month, on the sixth month, and at the end of treatment period.

### Study end

At study completion, a questionnaire will be given that includes questions related to patient satisfaction with the treatment received, the type of treatment patients believe they have received, and their expectations for improvement.

### Statistical analysis

The results will be analyzed by using the SPSS statistical software version 18.0. A descriptive analysis of the collected data will be obtained by using the mean, the standard deviation, and the maximum and minimum values for the quantitative variables that follow a normal distribution. For variables without a normal distribution (degree of pain, plasma levels, and quality of life, among others), the median, the 25th and 75th percentiles, and maximum and minimum values will be calculated.

Qualitative variables will be expressed as frequencies and percentages. Differences shall be detected by chi-square or Fisher tests for categorical variables and Student *t* or Mann-Whitney tests for the resultant variables.

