### Participants

Participants will be selected from a population with knee chronic pain caused by OA (>3 months in duration), from the communities of the island of Mallorca (Balearic Islands, Spain). These participants will be recruited in the outpatient clinics of the island’s hospitals and advertisements in local newspapers and through the hospital website (http://www.hsll.es). Advertisements for patient recruitment will not specify acupuncture as one of the treatments being investigated or offered. Doctors from the trauma services of local hospitals will be invited to screen patients. The clinical trial will be performed by the Pain Unit at Son Llàtzer Hospital, Palma de Mallorca.

A total of 160 patients will be necessary (80 subjects for each treatment group) to detect differences of at least three points in the pain perception assessment according to VAS (scale of 0 to 10). Accepted values will be for an alpha risk of 1 % and beta risk of less than 5 % in a bilateral contrast as well as a value of 4 for the standard deviation (size effect of 0.75). It is assumed that 20 % of the trial patients will be lost to attrition. Patients will be included in the study by case-consecutive, non-probability sampling after responding to a recruitment visit to the Pain Clinic; then if they sign an informed consent form, they will be placed randomly into one of the treatment groups [30].

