### Variables

#### Main variables

The primary outcomes will be the changes from the baseline of the VAS and the Western Ontario and McMaster Universities Osteoarthritis Index (WOMAC) for pain at the completion of treatment at 12 weeks.

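### The primary pain comparison is left to an unadjusted Student t or Mann-Whitney test, which leaves baseline pain unused as a covariate and, on the Mann-Whitney branch, does not estimate the 3-point mean difference that sizes the trial

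*Protocol article*

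**What the plan says.** Under Main variables, the protocol defines its primary endpoints: "The primary outcomes will be the changes from the baseline of the VAS and the Western Ontario and McMaster Universities Osteoarthritis Index (WOMAC) for pain", assessed at 12 weeks. The Baseline visit section and Table 1 show that both scales are recorded at visit 0, before allocation.

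The Statistical analysis section names chi-square or Fisher tests for categorical variables, and Student t or "Mann-Whitney tests for the resultant variables". It mentions no model and no baseline covariate, and gives no rule for choosing between the two tests. Two sentences earlier, in the part on descriptive summaries, it reads: "For variables without a normal distribution (degree of pain, plasma levels, and quality of life, among others), the median" and quartiles will be reported.

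The Participants section sizes the trial "to detect differences of at least three points in the pain perception assessment according to VAS", with "alpha risk of 1 % and beta risk of less than 5" per cent, two-sided, SD 4, standardized effect 0.75 and 20% attrition. It does not say whether 4 is the SD of a single score or of the change. The operative hypothesis is also stated as three VAS points.

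**The concern.** The target and the sample size are a difference between two means in VAS points. The analysis section classes pain as non-normal, and the natural reading then sends the primary outcome to a rank test. That test addresses whether one arm's changes tend to be larger. By itself it gives no mean difference in points and no confidence interval to set against 3.

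A change score also fixes the regression slope on baseline at 1, whereas ANCOVA estimates that slope from the data. When the true slope differs from 1, the change score carries avoidable variance. Since baseline pain is already collected, the precision is given up for nothing. What is at stake is the width of the primary interval and, under one reading of the SD, a good deal of power.

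**Working it through.** **Inputs from the protocol (Participants section).** Difference 3, SD 4, two-sided alpha 0.01, beta 0.05, attrition 20%, 80 per arm.

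**Input not in the protocol.** The correlation rho between baseline and 12-week scores, and the ratio k of baseline SD to follow-up SD. I take rho from 0.3 to 0.7 and k from 0.5 to 1.25 as assumptions.

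**1. The plan's own figure.** n per arm = 2 × [4 × (2.576 + 1.645)/3]² = 63.3, so 64. Then 64/0.8 = 80 per arm, 160 in total. This reproduces exactly, and the calculation is an unadjusted comparison of two means. Power with 64 per arm is 95.2% by the normal approximation and 94.6% by the noncentral t.

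**2. Variance of the two analyses, equal SDs (k = 1, common SD s).**
- Change score: 2(1 - rho)s².
- ANCOVA: (1 - rho²)s².
- Ratio: (1 + rho)/2, so the reduction is (1 - rho)/2.

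| rho | Ratio | Reduction |
|---|---|---|
| 0.3 | 0.65 | 35% |
| 0.5 | 0.75 | 25% |
| 0.7 | 0.85 | 15% |

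**3. Unequal SDs.** The ratio becomes (1 - rho²)/(1 + k² - 2·rho·k), so the reduction is (k - rho)²/(1 + k² - 2·rho·k). It is never negative in large samples and is zero when rho = k. For rho from 0.3 to 0.7:

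| k | Reduction |
|---|---|
| 0.5 | 0% to 7% |
| 0.75 | 0.5% to 18% |
| 1 | 15% to 35% |
| 1.25 | 37% to 50% |

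Eligibility requires moderate or greater pain. That may narrow the baseline SD (k below 1), and the gain could then be close to nothing.

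**4. Power for 3 points, 64 per arm, alpha 0.01 (noncentral t, equal SDs).**

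| rho | SD 4 is of a single score: change score | SD 4 is of a single score: ANCOVA | SD 4 is of the change: change score | SD 4 is of the change: ANCOVA |
|---|---|---|---|---|
| 0.3 | 83.2% | 96.5% | 94.6% | 99.6% |
| 0.5 | 94.6% | 98.8% | 94.6% | 98.8% |
| 0.7 | 99.8% | 99.9% | 94.6% | 97.5% |

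**5. Interval width.** If SD 4 is the SD of change, the 99% half-width is 2.615 × 4 × √(2/64) = 1.85 points. With ANCOVA at rho 0.5 it is 1.85 × √0.75 = 1.60 points.

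**6. Cost of the rank test itself.** On normal data its relative efficiency is 3/π, which gives 93.5% power against 94.6% for the t test, a loss of about one percentage point.

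**The case against.** The strongest reply is that nothing here is invalid. Randomization protects both named tests, regression to the mean affects the two arms equally in expectation, and the trial is sized correctly for an unadjusted comparison of means. That stands. A reader might infer bias or an underpowered design, and the documents support neither. If SD 4 is the SD of change, the planned t test already has about 95% power.

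Other tempting readings also go too far:

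- **That the plan fixes Mann-Whitney for the primary outcome.** The non-normality sentence governs descriptive summaries and refers to the level of pain, not its change. Student t remains open, and it yields an unadjusted difference in points with an interval. The mismatch applies to the Mann-Whitney branch only.
- **That a rank test can say nothing in points.** A Hodges-Lehmann shift with an interval can accompany it. The protocol does not name one, and it equals a mean difference only under further assumptions.
- **That chance imbalance in baseline pain is left uncorrected.** A change score subtracts baseline in full. When the regression slope is below 1 it over-corrects.
- **That Mann-Whitney forfeits the planned power.** The loss is about one point on normal data, and on non-normal data a rank test can be the more efficient.
- **That 15% to 35% is an established gain, or 83% against 97% the typical contrast.** Both rest on assumed values of rho and equal SDs, and the power contrast is the least favourable case shown.
- **That separate tests at four visits are planned.** The text does not say so. The other visits are secondary, and the handling of missing data may properly sit in an analysis plan that is not shown.

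The reply does not remove the core of the point. The article itself states the tests and names no adjustment, so this is a stated choice and not a detail left for later.

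**Conclusion.** The point holds as one of precision and of fit between test and target. The protocol offers two unadjusted tests for its primary outcomes, hints at the one that does not estimate the quantity it is sized on, and makes no use of baseline as a covariate.

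The mismatch needs no assumption beyond the likely choice of Mann-Whitney. The size of the precision gain does depend on assumptions: 15% to 35% of the variance for rho 0.7 to 0.3 with equal SDs, and about 0% to 50% once the SD ratio may run from 0.5 to 1.25.

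In power, if SD 4 refers to change, about 95% rises to between about 98% and 99.6%. If it refers to a single score, power goes from 83% to 97% at rho 0.3 and from 95% to 99% at rho 0.5, with almost no difference at rho 0.7. It is worth correcting but does not threaten the validity of the trial.

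**What to change.** In the Statistical analysis section, name one primary analysis: ANCOVA of the 12-week VAS score on treatment group and baseline VAS, and likewise for WOMAC pain. With baseline in the model, analysing the score or the change gives the same treatment estimate, so the primary outcomes need not be redefined.

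Report the adjusted EA minus SA difference in points with a 99% confidence interval, matching the planning alpha. Keep Mann-Whitney as a sensitivity analysis, and do not let a normality check choose the primary test. A repeated-measures model over all visits with baseline as covariate is an optional alternative.

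If the expected gain is quoted, give it as (1 - rho)/2 under an assumed rho and equal SDs, and state whether SD 4 is that of a score or of a change.

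The cost is wording only. No new data, visits or patients are needed, and SPSS, already named, fits the model. The protocol describes recruitment as still under way, so the change can be made before the data are unblinded.

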## Discussion

The aim of the study is to measure the effectiveness of EA in alleviating OA knee pain. Effectiveness indicators should be the relief of pain, stiffness and functional disability of the knee, the improvement of quality of live and a reduction in medication use.

The principal challenge expected with this study is the difficulty of effectively blinding SA application in a manner that is believable or credible for the patient. For this reason, we will avoid using the terms “sham acupuncture” or “placebo” in the information letter and consent form. The attempt to blind the process will be done by explaining to the patient that a new pain treatment will be assessed and compared with other techniques (infiltrations and analgesic stimulation) and that the selected patients must have no history of acupuncture treatment. The literature reports that the non-penetrating SA method has been widely used and has also been validated for avoiding skin receptor stimulation in SA [36]. Disclosure of a patient’s group affiliation will be avoided so that they will not be able to share information among themselves or compare treatments. The only person who will have full knowledge of the applied treatment will be the acupuncturist, although he will remain blind to the rest of the details of the study.

A satisfaction questionnaire will be completed at the end of the study to assess whether the patients believe they have or have not received treatment. To avoid introducing bias that could be caused by the interference of the circadian rhythm in the beta-endorphin and cortisol levels, patients will always be scheduled for blood sampling at the same hour.

As has been shown, it would seem clear that the treatment of knee OA must be a multidisciplinary approach, as there is currently no treatment alone that may be considered beneficial in absolute terms.

Although there are studies showing the efficacy of acupuncture for the treatment of OA pain, the lack of a common methodology to apply the treatment design complicates the comparison of the results between studies.

In this article, we combine all of the methodological suggestions for acupuncture studies, attempting to minimize the biases that may result from study design. We intend to make a comparison with a placebo that would allow the hypothesis to be validated.

We must not forget the current economic circumstances that drive us to look for therapies that are cost-beneficial for both the patient and the health system. In this direction, there are studies that suggest acupuncture as a cost-effective therapy for the treatment of knee OA.

Finally, sufficient evidence about the different physiological mechanisms would encourage further research on how acupuncture can relieve pain. However, the effect of acupuncture on the HPA system is not clear, and therefore we intend to provide more information that would clarify its function.

### Trial status

The trial is currently in the recruitment phase. Participant recruitment started in January 2015 and is expected to end in December 2015.

## Abbreviations

EA: Electro-acupuncture
EO: Endogenous opioid system
GADS: Goldberg Anxiety and Depression Scale
Group A: Experimental group
Group B: Control group
HPA: Hypothalamic-pituitary-adrenal
OA: Osteoarthritis
OARSI: Osteoarthritis Research International
SA: Sham acupuncture
SF-36v2: Short Form 36 version 2 health survey
TCM: Traditional Chinese Medicine
VAS: Visual analogue scale
WOMAC: Western Ontario and McMaster Universities Osteoarthritis Index
